#### Primary outcome

The Positive and Negative Symptom Scale (PANSS) will be used to measure overall symptom severity PANSS_T_, and severity of positive (PANSS+), negative (PANSS-) and general (PANSS_G_) psychopathology symptoms [55]. The PANSS has sound psychometric ratings in terms of both validity and reliability [56]. It has been widely used as an outcome measure in clinical trials for psychotic disorders. In the current study, change from baseline to week 26 on the PANSS_T_ score is the primary outcome measure.

#### Secondary outcomes

Secondary outcomes will include symptomatology, functioning and QoL, neurocognition, neuroimaging, substance use and biological correlates.

##### Symptomatology

The PANSS+, PANSS- and PANSS_G_, subscales will be used to assess positive and negative psychotic symptoms, and general psychopathology, respectively. Depressive symptoms will be assessed using the Montgomery-Åsberg Depression Rating Scale (MADRS [57];). The Clinical Global Impressions – Severity of Illness (CGI-S; 59) is a brief interviewer-rated scale that measures illness severity. The Clinical Global Impressions – Improvement (CGI-I [58];) is also an interviewer-rated scale and indexes the patient’s improvement or worsening relative to the baseline. The Patient Global Impressions – Improvement (PGI-I [59];), which is commensurate with the CGI-I, will be used as a self-report measure of perceived change since commencing treatment.

##### Functioning and quality of life

The Social and Occupational Functional Assessment Scale (SOFAS [60];) will be used to assess level of social and occupational functioning and is not directly influenced by the overall severity of the individual’s psychological symptoms. The Sheehan Disability Scale (SDS [61];) is a brief self-report tool developed to assess functional impairment in three inter-related domains; work/school, social and family life.

The Simple Physical Activity Questionnaire (SIMPAQ [62];) will be used to measure physical activity over a 7-day period around various assessment time pints. The SIMPAQ is a brief 8-item interview covering time spent in bed, sitting or lying down, walking, exercise, sport and other activities.

Social inclusion will be measured using the self-report questionnaire Social Inclusion in Mental Illness – Long Edition (SIMI-LE [63];). The SIMI-LE covers five inter-related domains: (1) housing, neighbourhood and services, (2) relationships, activities and setbacks, (3) employment and education, (4) finances and (5) health and wellbeing.

The Assessment of Quality of Life – 8 dimensions (AQoL-8D [64];) will be used as a measure of health-related QoL. The AQoL-8D was selected to assess units of quality-adjusted life years, enabling the quantification of the economic benefit of treatment.

##### Neurocognition

Neurocognition will be assessed using a variety of standardised, computer-based and pencil-and-paper tasks. Intellectual functioning will be assessed using the two subtest version Wechsler Abbreviated Scale of Intelligence – Second Edition (WASI-II [65];). The Cogstate computerised assessment battery will include Detection, Identification and *n*-back (1-back and 2-back) tasks. The Detection test measures processing speed using a simple reaction-time paradigm, the Identification test measures attention and processing speed using a choice reaction time paradigm, and the *n*-back tests measure visual working memory. Cogstate has demonstrated test-retest reliability and responsiveness, small practice effects, no significant floor or ceiling effects, and is an ideal measure to assess changes in neurocognition over time. Pencil-and-paper tests include: Symbol Digit Modalities Test (SDMT [66];) as a measure of visual attention and processing speed; Digit Span [67], a subtest of the Wechsler Adult Intelligence Scale designed to assess auditory-verbal attention span and working memory; and, the Rey Auditory Verbal Learning Test (RAVLT [68];) for the assessment of verbal learning and memory.

##### Neuroimaging

Participants will complete a 1-h magnetic resonance imaging MRI session on a 3-T Siemens Magnetom Skyra scanner at The Melbourne Brain Centre, Heidelberg, at two visits: (1) baseline and (2) end week 26. We will acquire structural, spectroscopy (GSH) and functional resting state, as follows:

High-resolution structural data will be acquired with a T1-weighted magnetisation-prepared rapid-acquisition gradient echo (MPRAGE) volumetric sequence.

Brain GSH concentration will be measured using a single-voxel MEscher-GArwood Point-RESolved Spectroscopy (MEGA-PRESS) spectral-editing sequence. A single voxel will be placed in the left anterior cingulate. This region has the advantage of showing GSH reductions in schizophrenia [69], being a major hub region for brain connectivity, and being relatively easy to shim.

Functional resting state MRI data will be acquired in the axial plane using a T2*-weighted echo-planar imaging sequence. Data will be acquired for approximately 10 min, during which time the participant will be asked to keep their eyes open and focussed on a fixation cross in the middle of the screen, but to allow their minds to wander.

For all sequences except the functional resting state participants will be asked to lie still and relax, and will have the option of listening to music or watching a DVD. Following the scans, a radiologist will review all images to assess whether there is any abnormal pathology. They will complete a report for each scan session and send this to the study’s designated physician/registrar. In the rare event that further investigation is required, the treating physician/registrar will contact the participant and discuss the radiological findings and refer on as needed.

##### Biological correlates

Measurement of inflammatory, oxidative and nitrosative stress markers will provide evidence of the drivers of neuroprogression and clarify the neuroprotective mechanism of NAC [3]. Approximately 25 mL of blood will be taken at baseline, at the 26-week treatment endpoint, and at 52-weeks’ follow-up. Cytokines associated with acute and chronic inflammation will be assessed. Markers of oxidative and nitrosative stress will also be analysed. Other markers may also be investigated if evidence of their involvement in these processes is demonstrated.

Participants will also be invited to provide a further 2.5-mL sample of blood (using the PaxGene™ tube) for analysis of genetic variation, and to identify the relationship between gene expression and treatment response, or medication side-effects.

#### Other measures

##### Cohort characteristics

Demographic data (sex, gender, age, living arrangements, educational level and employment status), medical and physical history, and medications, will be collected at screening with items sourced from Orygen’s harmonised questionnaire battery [70].

##### Diagnosis

Diagnostic information will be obtained using a number of measures. The Structured Clinical Interview for DSM-5 Research Version (SCID-5-RV [71];) modules pertaining to mood, psychosis, substance use and anxiety will be administered [71]. Because of the potential phenomenological overlap and difficulties of differential diagnosis of personality disorders (especially borderline personality disorder, BPD) and FEP [72], all the BPD items of the Structured Clinical Interview for DSM-IV Axis II Disorders Personality Questionnaire (SCID-II PQ [73];) will be administered. The 25-item Personality Inventory for DSM-5 brief form (PID-5-BF [74];) will be administered for a dimensional assessment of personality.

##### Medication adherence

The 10-item Medication Adherence Rating Scale (MARS, [75]) will be used to determine compliance with antipsychotic and trial medications. Compliance with the trial medications will also be determined by using a monthly pill count and can also be delineated from MRS and blood biomarkers.

##### Substance use

The Alcohol, Smoking and Substance Involvement Screening Test (ASSIST [76];) is a self-report measure for detecting and managing substance use and related problems in primary and general medical care settings. An overview of recent consumption and associated problems is obtained.

##### Physical health measures

Physical health measurements include weight, height, waist circumference, blood pressure and heart rate, and will be assessed at baseline, 4 weeks, 8 weeks, 12 weeks, 26 weeks and 52 weeks. These measurements will be completed by trained study team members.

### Determination of sample size

Previously, moderate effects have been observed (Cohen’s *d* = 0.57) in those who received NAC on global symptom outcomes over a 24-week period [37]. We have elected to use a conservative estimate of effect of 0.45 (Cohen’s *d*) for between-group differences on the PANSS_T_ score. With power (1 − β) set at 0.80, alpha (α) set at .05, and a one-tailed test we would need a total sample size of 124 (62 per group). Allowing for attrition rate of 30%, we calculate that we would need a total sample size of 162 (81 per group).

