### Assignment of interventions

#### Randomisation

Participant eligibility will be established before randomisation. Participants will be assigned randomly and consecutively in a 1:1 ratio to one of two interventions, NAC or placebo. The randomisation sequence will be based on a computer-generated, permutated, block randomisation scheme with stratification for site. The randomisation sequence will be computer-generated by a statistician who is independent of the day-to-day conduct of the trial. The allocation sequence will be concealed within the RPMS.

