#### Statistical methods

Statistical analyses will follow the International Conference on Harmonisation E9 statistical principles. Reporting of results will be done in accordance with Consolidated Standards of Reporting Trials (CONSORT) guidelines [77]. All participants who were randomised and who have at least one post-baseline observation will be included in a modified intent-to-treat analysis [78]. All attempts will be made to ensure that all participants have follow-up data even if they discontinue from the treatment. The primary efficacy analysis will assess average treatment group differences for the primary outcome measure (PANSS_T_) over the entire study period and will use a likelihood-based mixed-effects model, repeated-measures approach (MMRM). The MMRM model includes the fixed, categorical effects of treatment, visit, treatment-by-visit interaction, and Region (Parkville and Sunshine) will also be included as a factor in the model. Antipsychotic dosing may be also used as the covariate in the model. The MMRM includes all available data at each time point and is the preferred method of analysing clinical trial data in psychiatry as compared to more traditional repeated measures analysis of variance and analysis of covariance models. Planned comparisons will be done with the MMRM models to determine between-group differences in change in symptom measures from baseline to week 26. Differences between treatment groups in terms of secondary outcome measures will be examined using MMRM as per the primary outcome. Correlational analyses as well as multilevel modelling will be used to develop a better understanding of how changes in blood- and brain-derived biomarkers relate to symptoms, functioning and neurocognition. No interim analyses will be conducted.

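### The 80% power rests on an unjustified one-tailed 5% test: two-sided it is about 70%, and a separate attrition slip takes it to about 66%

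*Protocol article*

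**What the plan says.** All the design parameters are in the protocol article under Determination of sample size. The effect is introduced with "We have elected to use a conservative estimate of effect of 0.45" (Cohen's d, for the between-group difference in PANSS total), which is lower than the 0.57 reported from an earlier NAC trial. Power is "set at 0.80, alpha" is "set at .05, and a one-tailed test", and the result is "a one-tailed test we would need a total sample size of 124 (62 per group"). The inflation follows: "Allowing for attrition rate of 30"%, "we calculate that we would need a total sample size of 162 (81 per group"). Under Randomisation, allocation is 1:1.

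The Background states the primary hypothesis directionally: lower PANSS total on NAC than on placebo at week 26. Under Statistical methods the article names a repeated-measures mixed model (MMRM) with a planned comparison of change from baseline to week 26. It gives neither a significance level nor a sidedness for that comparison. The sample-size paragraph is therefore the only place in the article where an error rate is attached to the primary comparison.

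**The concern.** A one-tailed test at 0.05 is the same test, in the direction favouring NAC, as a two-sided test at 0.10. It doubles the chance of a false claim of benefit from the 2.5% that a conventional two-sided 5% test allows, and the article gives no reason for this.

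The direction is not so well established that it could go without saying. The Background reports that the only previous NAC trial in early psychosis found no difference between groups on its primary negative-symptom outcome, on positive or general symptoms, or on functional outcomes. A directional hypothesis states what the investigators expect. It does not by itself justify a looser error rate.

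The practical consequence is a grey zone. With a one-sided p between 0.025 and 0.05, the two-sided p lies between 0.05 and 0.10. The trial would then succeed by the sample-size rule while its 95% confidence interval for the PANSS difference includes zero. If the result is instead judged two-sided, the power is lower than the figure a reader takes from the article.

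**Working it through.** **Inputs, all from the article:** d = 0.45 (so SD = 1), alpha 0.05, one-tailed, power 0.80, 1:1 allocation, attrition 30%, 162 randomised (81 per group).

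**Step 1: reproduce the article's figure.** Per group, n = 2(z₁₋α + z₁₋β)²/d².
- One-tailed: 2 × (1.645 + 0.842)²/0.45² = 61.1, rounded up to 62. The noncentral t calculation gives 61.75, also 62. Total 124, as stated.
- Two-sided: 2 × (1.960 + 0.842)²/0.45² = 77.5, so 78 per group; the noncentral t gives 78.5, so 79 per group (158 in total).

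Only the one-tailed test reproduces 124.

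**Step 2: effect of sidedness alone, 62 per group.** The noncentrality is d√(n/2) = 0.45 × √31 = 2.505.
- One-tailed: Φ(2.505 − 1.645) = 80.5%; noncentral t 80.1%.
- Two-sided: Φ(2.505 − 1.960) = 70.7%; noncentral t 70.1%.

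Sidedness costs about 10 percentage points.

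**Step 3: the attrition step, a separate matter.**
- What was done: 124 × 1.30 = 161.2, rounded up to an even 162.
- What 30% loss requires: 124/(1 − 0.30) = 177.1, which is 178.
- What 162 leaves after 30% loss: 162 × 0.70 = 113.4 completers, or 56.7 per group.
- Loss at which 162 still leaves 124: 1 − 124/162 = 23.5%.

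**Step 4: power with 56.7 per group.** The noncentrality is 0.45 × √28.35 = 2.396.

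| Completers per group | One-tailed 5% | Two-sided 5% |
|---|---|---|
| 62 | 80.1% | 70.1% |
| 56.7 | 76.9% | 66.1% |

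(Noncentral t; the normal approximation is less than 1 point higher in every cell.) With 56.7 per group the effect detectable with 80% power, two-sided, is d = 0.53. To have 80% two-sided power at d = 0.45 after 30% loss would take 79/0.70 = 112.9, so 113 per group or 226 randomised.

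**Step 5: possible gain from baseline adjustment.** The article gives no correlation between baseline and week-26 PANSS total, so this is an assumption shown over a range. If d is on the week-26 score scale, adjustment raises the effective effect to d/√(1 − ρ²). With 56.7 per group, two-sided 5%:

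| Assumed ρ | Effective d | Power |
|---|---|---|
| 0 | 0.450 | 66% |
| 0.3 | 0.472 | 70% |
| 0.5 | 0.520 | 78% |
| 0.6 | 0.563 | 84% |
| 0.7 | 0.630 | 91% |

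The article does not say which scale d refers to. If it is the change-score scale, the gains would differ.

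**The case against.** The strongest defence is that the one-tailed test is disclosed, agrees with the directional hypothesis, and is computed correctly. That stands: 124 is not a miscalculation, and the 80% is true on its stated condition. What remains is that the condition is unusual, doubles the error rate in favour of NAC, and is not defended.

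A reader might infer that the article contradicts itself, because the analysis section says "Statistical analyses will follow the International Conference on Harmonisation E9 statistical principles" and never mentions a one-sided primary test. The documents do not support that. Nothing in the article calls the primary test two-sided, and sidedness may properly be left to the statistical analysis plan. The general commitment to those principles settles nothing that can be checked here, and the F and t tests mentioned for the imaging data say nothing about the PANSS contrast.

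A reader might also put the whole fall from 80% to 66% down to the one-tailed test. That is wrong. Sidedness accounts for 80% to 70%; the rest comes from the attrition arithmetic, which takes the one-tailed test itself from 80.1% to 76.9%.

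It is also too strong to say that the trial will be underpowered. The figures are for a t-test in completers. The planned MMRM uses partial data, follow-up is sought after treatment discontinuation, and baseline adjustment could restore 80% or more if the correlation is about 0.6 or higher. This objection stands as to the trial's eventual power. It does not rescue the stated figure, which takes no such credit.

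Finally, a detectable effect of 0.53 does not show that 0.45 was wrongly called conservative. The assumed value is conservative relative to 0.57; the detectable effect is a different quantity.

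**Conclusion.** The point holds as two distinct shortfalls in one stated power. First, the 80% depends on a one-tailed 5% test for which no reason is given; at two-sided 5% the same 62 per group has about 70% power. Second, the inflation for attrition multiplies by 1.30 instead of dividing by 0.70. The 162 randomised therefore yield about 113 completers, with about 77% power even on the article's own one-tailed terms and about 66% two-sided.

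These figures assume d = 0.45, equal groups, exactly 30% loss and no gain from covariates, repeated measures or partial data. The sidedness point concerns an unjustified design choice. The attrition point is an arithmetic error, and it holds whichever test is used.

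**What to change.** Before unblinding, specify the week-26 contrast in PANSS total as a two-sided 5% test (equivalently one-sided 2.5%), reported with a 95% confidence interval. The article plans no interim analyses and keeps the biostatistician blinded, so the choice can still be made without any suspicion that the data drove it.

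Restate the power for 162 randomised with 30% attrition: about 66% at d = 0.45, or 80% at d = 0.53, with no covariate gain. Correct the inflation step, stating that 124 completers at 30% loss would need 178 randomised. If credit is claimed for adjusting for baseline PANSS, give the assumed correlation, the scale of d, and a range such as 70% at 0.3 to 91% at 0.7.

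The cost is wording and a less favourable stated power. No patients are added. Restating the power does not restore it: holding 80% two-sided at d = 0.45 with 30% loss and no covariate gain would need about 226 randomised, which is not proposed here.

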**Methods/design:**

ENACT is a 26-week, randomised controlled trial of adjunctive NAC versus placebo, with a 26-week non-treatment follow-up period, for FEP. We will be recruiting 162 young people aged 15–25 years who have recently presented to, and are being treated at, the Early Psychosis Prevention and Intervention Centre, Melbourne, Australia. The primary outcome is the Total Score on the Positive and Negative Syndrome Scale which will be administered at baseline, and weeks 4, 8, 12, 26 (primary endpoint), and 52 (end of study). Secondary outcomes include: symptomatology, functioning, quality of life, neurocognition, blood-derived measures of: inflammation, oxidative and nitrosative stress, and magnetic resonance spectroscopy measures of glutathione concentration.

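### The 30% attrition allowance multiplies by 1.30 instead of dividing by 0.70, so 162 participants do not give the stated 80% power

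*Protocol article*

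**What the plan says.** The section on determination of sample size in the protocol article sets out the whole calculation. On the effect, the text reads "We have elected to use a conservative estimate of effect of 0.45" (Cohen's d, between-group difference in PANSS total). Power is 0.80 and alpha is "set at .05, and a one-tailed test". From these inputs "we would need a total sample size of 124 (62 per group"). The attrition step follows: "Allowing for attrition rate of 30%, we calculate that we would need a total sample size of 162 (81 per group"). The Methods/design part of the Abstract carries the result forward as the recruitment target: "We will be recruiting 162 young people aged 15–25 years". Allocation is 1:1 (Study design and ethical approval).

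**The concern.** An attrition rate is the share of those enrolled who are later lost. To finish with a required number, that number is divided by the proportion retained. Adding 30% to the required number is a different operation, and it protects against a smaller loss. Here 162 is what results from adding 30%.

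At stake is whether the trial's size supports the power claimed for its primary outcome. If the allowance is wrong, the required 124, the 30% and the 162 are inconsistent with one another. A reader who relies on 80% power at 30% attrition is then relying on something the figures do not deliver.

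**Working it through.** **Inputs**, all from the sample-size section: d = 0.45; power 0.80; alpha 0.05, one-tailed; 124 in total (62 per group) before attrition; attrition 30%; 162 in total (81 per group) after attrition.

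**Step 1: reproduce the base figure.** For two equal groups, the normal approximation is n per group = 2(z₀.₉₅ + z₀.₈₀)² / d² = 2(1.645 + 0.842)² / 0.45² ≈ 61.1, rounded up to 62. The noncentral t gives 61.75, also 62. Power at 62 per group is 80.1% (noncentral t). The stated 124 is correct on its own inputs. A two-tailed test would need 78 (normal) or 79 (t) per group, so the base is one-tailed, as stated.

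**Step 2: reproduce the inflated figure.**

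| Operation | Total | Per group |
|---|---|---|
| Multiply by 1.30 | 124 × 1.30 = 161.2 → 162 | 62 × 1.30 = 80.6 → 81 |
| Divide by 0.70 | 124 / 0.70 = 177.1 → 178 | 62 / 0.70 = 88.6 → 89 |

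The stated 162 (81 per group) matches the first row exactly. The second row is the one that allows for 30% attrition. The difference is 178 − 162 = 16 participants, and 16 / 178 = 9%.

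**Step 3: what 162 delivers at 30% attrition.** 162 × 0.70 = 113.4 in total, or 56.7 per group. That is 124 − 113.4 = 10.6 fewer than required. With d = 0.45 and one-tailed 0.05:

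- normal approximation: 0.45 × √(56.7 / 2) − 1.645 = 0.751, so power is 77.4%;
- noncentral t: power is 76.9%.

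The effect detectable with 80% power at 56.7 per group is d = 0.47.

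**Step 4: the attrition that 162 can absorb.** 1 − 124 / 162 = 23.5%, that is, 38 of 162 participants.

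**The case against.** The strongest counter-argument is that participants who leave early are not lost to the analysis. The Statistical methods section plans a mixed model for repeated measures on everyone randomised with at least one post-baseline observation, and intends to follow up those who stop treatment. Table 1 schedules the PANSS at weeks 4, 8 and 12 before week 26. The 77% is therefore the power of a comparison limited to participants observed at the endpoint, and the planned analysis may do better.

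How much better depends on a within-subject correlation r that the document does not give. As an illustration, assume every participant missing at week 26 has a week-12 score. The effective number per group is then 1 / [(1 − r²)/56.7 + r²/81], which is about 58 at r = 0.3, 61 at r = 0.5, 64 at r = 0.6 and 67 at r = 0.7. It reaches 62 at r ≈ 0.53. If only half of the dropouts have such a score, r must be about 0.70.

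This point stands as a qualification: the model could recover part or all of the loss. It does not rescue the sentence. The sample-size section is a plain two-group calculation with an explicit attrition allowance. It takes no credit for partial data and states no correlation.

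Two further points are fair. First, the section does not say at which visit the 30% applies; if it means week 52, loss at the week-26 primary endpoint could be smaller. Second, a shift in detectable effect from 0.45 to 0.47 is small beside the choice of 0.45 itself, which was reduced from an observed 0.57. Both bear on how serious the error is, not on whether it is one. Reading the 30% as planned over-recruitment does not help either: the stated attrition rate would then be wrong and should be about 23%.

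**Conclusion.** The concern holds. The base requirement of 124 is right, but the allowance added to it is not: 162 comes from multiplying by 1.30, whereas 30% attrition requires 178. Under the paragraph's own two-group method, 162 with 30% lost leaves about 113 participants and 77% one-tailed power, about 3 points below the stated 80%.

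This rests on three assumptions: the 30% is the proportion of randomised participants without the week-26 outcome, those participants contribute nothing to the comparison, and the one-tailed test is taken as stated. The effect on the trial is modest, and neither the endpoint nor the analysis model is affected. It is nonetheless a definite error in the figure that justifies the trial's size.

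**What to change.** Correct the last sentence of the sample-size section. Show the standard inflation, 124 / (1 − 0.30) = 177.1, giving 178 (89 per group), and then describe what 162 provides in one of two ways:

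- 162 gives 80% power (one-tailed) provided attrition by week 26 is no more than 23%; or
- at 30% attrition by week 26, 162 leaves about 113 participants and about 77% power (one-tailed) in a comparison of those observed.

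Naming the visit to which the attrition rate applies removes a further ambiguity. If the sponsor wants credit for partial follow-up under the mixed model, the section should say so and give the assumed correlation and dropout pattern.

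The cost is one sentence and a slightly less favourable statement of power or tolerated attrition. No extra enrolment is needed, and the 162 in the Abstract can stay. Raising the target to 178 instead would need 16 more participants, about 16 weeks at the forecast rate of one per week in the Study setting section, and the Abstract would have to change too.
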